### 1.1.2 Patient circuit

A basic primary-level NCD service was initially introduced at each clinic. The typical patient circuit is as follows: patients are directed at reception to the MSF NCD service if they have both a medical indication (suspected or confirmed target NCD or risk factor) and a social indication (Syrian refugee or vulnerable Jordanian). All other cases are directed to the standard MoH (or private) primary care service.

Patients are initially triaged by nurses who record socio-demographic data; measure height, weight, waist circumference, blood pressure, heart rate, capillary blood sugar level, temperature and oxygen saturations; and calculate body mass index. Doctors provide medical consultations according to setting-specific protocols. These were initially based on Jordanian and international guidelines and were later adapted in line with MSF Operational Centre Amsterdam (MSF-OCA) NCD guidelines (see section 1.1.3 for more detail).

At first visits, doctors record a complete medical, medication and family medical history and perform a clinical examination for each patient. Lifestyle CVD risk factors (smoking status, alcohol intake, exercise levels) are recorded; global cardiovascular risk score is calculated; acute complications are identified and treated; long-term medications are prescribed for symptom management and secondary prevention of complications; patients are referred for laboratory testing; and a follow-up interval is determined. Patients with specific needs are referred internally (see below) or externally to the Jordanian public health services or to other NGOs, as described earlier.

Follow-up visits involve review of patients’ symptoms and disease control, vital signs, laboratory results; determination and recording of new diagnoses; adjustment and / or initiation of medications; and referral for further laboratory tests or to other health providers as required. Doctors also cover health education at each consultation and refer all patients to the programme health promoters.

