### 1.1.3 MSF NCD Clinical Guidelines

MSF-OCA has developed a new NCD Guideline to address the lack of standard guidelines on non-communicable disease management in humanitarian settings within MSF and elsewhere (http://hdl.handle.net/10144/618798). This provides programmatic and evidence-based clinical guidance for NCD management, addressing diagnosis; clinical examination; patient education regarding the disease, lifestyle modification and self-management of their illness; targets for disease control; medical management in including the assessment and management of global cardiovascular risk; management of acute and chronic complications; and onward referral. The conditions covered are: asthma, chronic obstructive pulmonary disease, diabetes, hypothyroidism, epilepsy, cardiovascular disease and hypertension, renal impairment, cancer and psychiatry. The guideline is currently being field-tested in MSF programmes in diverse settings but, to date, it has not been formally evaluated. Current indicators and outcome measures used by the programme are listed in Table 1 below.

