**Table 1. Standard epidemiological and quality indicators for MSF NCD services**

### 1.1.4 Evolution of model of care

| **Epidemiological / service activity indicators** | **Quality indicators** |
| --- | --- |
| Number / % of new patient consultations per month | Number / % of DM patients that have micro-albuminuria or urinary protein testing in the last year (Target = 80%) |
| Number / % of follow-up consultations per month (% of total visits) (by age, gender, nationality) | Number / % of patients with DM or on ACE inhibitor (ACEi) with Creatinine testing in last year (Target 80%) |
| Number/ % of patients presenting with the following morbidities: DM Type I, DM Type II, Hypertension,  other CVD, Asthma, COPD, Hypothyroidism, other | Number/ % asthma and COPD patients who receive control review (spirometry or clinical) in last year (Target = 80%) |
| Number of new diagnoses over a period of time | Number/% of asthmatics with acute exacerbations/ admissions in last year (Target = 20%) |
| Number/ % of exits per month: % defaulter, % dead (by primary diagnosis),  % self-transferred, % other | Number / % of DM patients/ hypertensives with mean BP <= 140/90 over last 12 months  (Target = 80%) |
|  | Number / % of DM patients with mean HbA1C < 8.0 % (or average FPG<150) in last 12  months (Target = 80%) |

Programmatic changes over time include introduction of: (1) a home visit team (2) a humanitarian liaison officer and (3) a formal MHPSS service. Technical changes introduced over time include: (1) task shifting to nurses of follow-up consultations (2) introduction of MSF-OCA NCD Guidelines and (3) implementation of spirometry. Contextual changes that occurred since programme inception include: (1) introduction of co- payments by the Jordanian government for Syrian refugees accessing MoH primary care services in November 2014 (2) increased recruitment of vulnerable Jordanians to the MSF NCD programme in the last quarter of 2015 and (3) closure of the MSF NCD programme to new patients from May to October 2016.

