### 1.1.6 Existing data sources, records and assessment processes

Routine cohort data are recorded in a paper-based patient file and entered daily into a purpose-designed MS Excel database by a trained data entry operator. The demographic data collected include: age, gender, mobile phone number, highest level of education; country of origin; refugee status and governorate of origin if Syrian; and insurance status if Jordanian. Data on Syrian refugees’ date of arrival in Jordan, UNHCR registration and Ministry of Interior card status are also collected if appropriate. Socio-demographic data are recorded on household size and crowdedness, type of dwelling and household makeup including gender and highest level of education attained by household head. Factors affecting treatment access and adherence are also documented i.e. impaired mobility and whether living with a treatment supporter.

Clinical data collected at the patient’s first visit include medical history, family history of relevant NCDs, lifestyle factors (smoking, alcohol consumption and exercise levels) and baseline vital signs (BMI, waist circumference, blood pressure, heart rate, blood sugar level and cardiovascular risk score assessment). New diagnoses; numbers, types, doses and reason to adapt medications; recommended specialist referral; and referral for laboratory tests are recorded at the first and each subsequent clinical visit.

At review visits, nurses record repeat vital signs and laboratory results; health educators record current exercise levels, smoking status and current stage of change on the Prochaska and DiClemente stages of change model for behaviour change. Symptom and functionality scores are recorded before and after a course of individual counselling, using Generalized Anxiety Disorder 7-item Scale (GAD7), Patient Health Questionnaire for Depression (PHQ 9) and a locally devised four-item screening tool for PTSD. These tools will be revised in early 2017.

Operational data recorded include numbers of new and follow-up medical consultations per month, type of consultation (nurse, doctor, home visit team), number of referrals made, number of health education sessions attended and programme exits (death, defaulter, voluntary defaulter). The number of MHPSS discussion groups, psycho-education sessions and individual counselling sessions undertaken per month are also recorded.

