| “Effectiveness”/ Quality of Care  What are the trends in clinical outcomes and quality indicators of the programme?  What are the perceived benefits/unintended consequences from a patient and provider perspective? | Clinical Outcomes | No./% patients with hypertension that have a most recent BP <= 140/90 6 and 12 months post enrolment and trend from baseline  Number / % of patients with diabetes that have a most recent BP <= 140/90 6 and 12 months post enrolment and trend from baseline  Number / % of patients with diabetes with last HbA1c < 8.0 %/ 7.0 % 6 and 12 months post enrolment and trend from baseline  Number/% with a reduction of >= 0.5 mmol/L in cholesterol level from baseline 6 and 12 months from enrolment  Number/% of patients with asthma / COPD free from exacerbations/ admissions in the previous 6 months  Number / % of patients who report decreased/quitting smoking within reporting period  Number / % of patients who report increased levels of exercise from baseline during reporting period  Trend recommended referrals to another facility for acute complications/specialist care, as a proportion of active cohort | Routine facility cohort data  Costing data (for incremental costing analysis)  2 Focus group with patients  Semi-structured interviews with approximately 12 clinic staff and 16 patients |
|  | Quality Indicators | Proportion of recommended referrals to other services that are appropriate as per guideline  Number/ % of active patients with CVD prescribed a statin during reporting period  Number/ % of patients with CVD prescribed aspirin during reporting period  Number/ % of patients with CVD prescribed at least one anti-hypertensive during reporting period  Number/% of patients with COPD/asthma with inhaler technique check documented  Number/ % of times when appropriate clinical action taken based on clinical or laboratory findings according to guideline (see Annexe 2d for detail)  Trend in defaulters as a proportion of active cohort during reporting period  Description of cohort deaths (patient characteristics) | Clinical audit  Participant observation  Routine health facility cohort data |
|  | Perceived Effectiveness | Patient and providers perspectives on effectiveness of programme components (clinical review, medications, HE, HLO, MHPSS, HV) | Key informant interviews  2 Focus groups with patients  Semi-structured interviews with 12 MSF/clinic staff and 16 patients |

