## 3.3 Study population

The study population for this evaluation consists of four groups:

1. The broader study population, which was included in the pre-existing, completed cross-sectional household survey, consisted of UNHCR-registered and unregistered Syrian refugees living outside of official camp settings within Irbid governorate.

2. Patients enrolled in MSF’s NCD clinics:

This refers to non-camp-dwelling Syrian refugees and vulnerable Jordanians who have been enrolled in MSF’s vertical NCD clinics in Irbid, Jordan, since patient registration was introduced in December 2014. To date (November 2016), 4672 NCD-related patients (aged 1 to 94 years) have been registered in the two clinics. Inclusion criteria are (1) Socio-demographic [Syrian refugee, refugee from another origin or vulnerable Jordanian (defined as patients who were identified as vulnerable according to the Ministry of Social Development National Aid Fund list)] and (2) Medical [confirmed CVD (including angina pectoris, myocardial infarction, ischaemic stroke, peripheral vascular disease), CVD risk factors (HTN), COPD, Asthma and/or DM]. Patients must fulfil both criteria.

The routine cohort data analysis, including the clinical audit, will include data from all enrolled patients aged six years and above (using files of patients admitted from January 2015 through to December 2016); qualitative data gathered through focus group discussions (FGDs) and semi-structured interviews (SSIs), and data from the adherence survey will be collected from a sample of adult patients aged 18 or older.

3. Clinic staff:

Semi-structured interviews will also take place with current and former healthcare workers and MSF management staff who provide(d), supervised or supported MSF NCD services in Irbid, Jordan.

4. Key Stakeholders:

Informal interviews will take place with key stakeholders, including members of the Jordanian Ministry of Health; Irbid District Health Office; clinical manager of the Ibn Sena MoH clinic where MSF‘s clinic is co-located; and Syrian refugee community leaders.

The eligibility criteria, recruitment and sampling methods are described further under each methodology’s sub-section below.

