### 3.4.1 Cohort study area and study population

The study location will be the two MSF-OCA supported clinics in Irbid city, northern Jordan. The first clinic was opened in December 2014 within an MoH primary care facility in Ibn-Sena and the second, opened in April 2015, works alongside a private organization, Arab Medical Relief (AMR), in their facility at Ibn-Rushd.

To date (November 2016), 4672 NCD-related patients (aged 1 to 94 years) have been registered in the two clinics, since patient registration was introduced in December 2014. Inclusion criteria are (1) Socio-demographic [Syrian refugee, refugee from another origin or vulnerable Jordanian (defined as patients who were identified as vulnerable according to the Ministry of Social Development National Aid Fund list) and (2) Medical [confirmed CVD (including angina pectoris, myocardial infarction, ischaemic stroke, peripheral vascular disease), CVD risk factors (HTN), COPD, Asthma and/or DM Type I or II]. Patients must fulfil both criteria. All NCD patients aged six years and older with at least two recorded visits (to enable evaluation of outcomes) will be included in the study cohort. This includes any new patients presenting with a new or existing diagnosis of a target NCD.

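### Table 2 scores blood pressure control in diabetes from age six against a single 140/90 cut-off, so children with pressure raised for their age count as controlled

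*Protocol*

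**What the plan says.** Table 2, under the clinical outcomes for effectiveness and quality of care, lists "Number / % of patients with diabetes that have a most recent BP <= 140/90" at 6 and 12 months after enrolment, with the trend from baseline. The data source is the routine facility cohort. The row has no age limit and no second threshold for children, and it does not refer to the clinical guideline.

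The cohort itself is not an adult one. Section 3.4.1 takes "All NCD patients aged six years and older with at least two recorded visits", and type I and type II diabetes are both entry diagnoses. Section 3.3 agrees: the routine data analysis "will include data from all enrolled patients aged six years and above". An adult line exists in the protocol, but only for other components. Section 3.3 says "data from the adherence survey will be collected from a sample of adult patients aged 18 or older", and the qualitative work has the same limit.

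Table 1 holds the programme's routine version of the indicator, "Number / % of DM patients/ hypertensives with mean BP <= 140/90 over last 12 months", again without an age limit. It averages over 12 months where Table 2 takes the latest reading. Section 1.1.3 says that the guideline includes "targets for disease control", but the guideline is not part of the protocol. Section 3.4.5 uses age as a regression covariate.

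**The concern.** A control indicator should separate patients whose blood pressure is acceptable from those whose pressure is not. For adults with diabetes, 140/90 can do that. For a child of six or ten it mostly cannot, because values that are high for that age generally lie well below it. This premise is general clinical knowledge; the protocol does not itself call 140/90 an adult threshold.

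Followed as written, the rule counts a child with diabetes as controlled at any reading up to 140/90. Children with normal pressure are counted correctly, so the error is confined to those who are raised for age but do not exceed the cut-off. Adjusting for age in a regression does not change who is counted.

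Two things are at stake, both modest. The pooled percentage is slightly too favourable, and the indicator is close to uninformative for the children in it. Section 3.4 gives blood pressure control as its own example of a disease-control target to be evaluated, so the percentage should be one that measures it.

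**Working it through.** No sample size, power or stated figure is attached to this indicator, so there is nothing of the plan's own to reproduce. The check has two parts.

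**1. Does anything in the protocol remove children from this row?**

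- Age floor: six years (sections 3.3 and 3.4.1).
- Diagnosis: type I or type II diabetes (section 3.4.1).
- Threshold: one value, 140/90 (Table 2; also Table 1).
- Adult restriction: adherence survey and qualitative samples only (section 3.3).
- Individualised target: given for HbA1c in section 3.4.2; none for blood pressure.
- Paediatric blood pressure criterion: none anywhere in the document.

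Nothing removes them.

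**2. How large could the error be?**

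Let *c* be the share of diabetes patients aged 6–17 and *m* the share of those children who are raised for age but at or below 140/90. Both are assumptions, because the protocol gives neither.

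Overstatement of the pooled percentage, in points = 100 × *c* × *m*.

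| | *c* = 1% | *c* = 3% | *c* = 5% |
|---|---|---|---|
| *m* = 5% | 0.05 | 0.15 | 0.25 |
| *m* = 10% | 0.10 | 0.30 | 0.50 |
| *m* = 20% | 0.20 | 0.60 | 1.00 |

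With more extreme assumptions the range widens: *c* = 0.5% and *m* = 5% give 0.025 points; *c* = 10% and *m* = 30% give 3.0 points.

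For scale, take an assumed 60% control and assumed numbers of diabetes patients. The 95% confidence half-width is 1.96 × √(0.6 × 0.4 / *n*):

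- *n* = 1,000: 3.04 points
- *n* = 2,000: 2.15 points

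Every value in the table is below both. The most extreme case (3.0 points) is about equal to the first and exceeds the second.

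**Trend from baseline.** If the children's pass rate does not change over time, the observed gain is the adult gain × (1 − *c*). An adult gain of 10 points then reads as 9.9, 9.7 or 9.5 points at *c* = 1%, 3% or 5%.

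**Case mix is separate.** With *c* = 5%, adults at 60% and every child passing, the pooled figure is 0.95 × 60 + 0.05 × 100 = 62%. Of that 2-point rise, only 100 × *c* × *m* (0.25 to 1.0 points here) is misclassification. The rest comes from children who are correctly counted as controlled.

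**The case against.** The strongest case on the other side is that the affected group is not shown to be of any size. The registered age range of 1 to 94 years covers all diagnoses, including asthma, and includes children under six whom the cohort excludes. The number of children with diabetes is unknown, and both inputs to the calculation are assumed. This stands, and it is why the magnitude can be given only as a range.

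The threshold's unsuitability for children also rests on knowledge from outside the protocol, and the unseen guideline may set paediatric targets. That is fair, but the row states its own number and does not defer to the guideline. The absence of a guideline reference proves little by itself, because the rows that carry one concern the appropriateness of actions and referrals, not clinical outcomes.

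It can be said that age strata for a secondary descriptive indicator belong in a statistical analysis plan. Here, however, the population, cut-off and time points are already fixed, and an analysis plan that followed them would carry the problem forward.

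Two further objections are correct. Restricting to adults may move the percentage more than the error does, because of case mix, so the all-age figure should stay alongside. The hypertension indicators also have no age limit. They are outside this point, and leaving them alone means the two blood pressure indicators would cover different age groups unless the team chooses to align them.

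**Conclusion.** The point holds, at low severity. As written, Table 2 counts children with diabetes as controlled whenever their latest reading is at or below 140/90, including those whose pressure is high for their age. On assumed child shares of 1–5% and assumed misclassified shares of 5–20%, the overstatement is 0.05 to 1.0 percentage points, and the trend is diluted by at most half a point in ten. This is one of the further outcomes that section 3.4.2 leaves to Table 2, not a principal one, and no conclusion of the evaluation depends on it.

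The conclusion rests on the text for the age range and the single cut-off, and on general clinical knowledge for lower blood pressure norms in childhood. Confidence in its practical importance is limited, because the protocol does not give the number of children with diabetes or their blood pressures.

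**What to change.** In Table 2, define the diabetes blood pressure indicator for patients aged 18 or older, the age line that section 3.3 already uses for the adherence survey and qualitative samples. Report the all-age figure beside it, so that the result can still be read against the routine indicator in Table 1. For ages 6–17, give the number of children and their mean or median blood pressure, without pass or fail against 140/90.

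Age- and sex-standardised values for the children are optional where height is on file. Section 1.1.2 has it measured at first triage: "Patients are initially triaged by nurses who record socio-demographic data; measure height, weight, waist circumference, blood pressure, heart rate". If they are used, the reference should be named.

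The cost is one age restriction, one extra figure and one small table. The restriction needs only age, which is already recorded (section 1.1.6: "The demographic data collected include: age, gender, mobile phone number"). The downsides are that the adult percentage will probably be slightly less favourable, the table for children will be small, and the adult figure alone is not directly comparable with the all-age routine indicator. Keeping the all-age figure deals with the last of these.

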Health promoters provide individually tailored health education at each clinical contact. Topics covered include: education about diagnosis and disease, treatment and adherence support, patient concerns and expectations, and lifestyle changes. Motivational interviewing techniques are used to support patients to make lifestyle modifications related to diet, exercise levels and smoking. On enrolment, the doctor and health educator see patients for thirty minutes each; patients on return visits spend approximately fifteen minutes each with clinical staff (either a doctor or nurse) and a health educator.

Routine laboratory tests are carried out at a local laboratory, which has been quality assured by MSF. At the first visit a urine dipstick (for white cells, red cells and protein) is performed. A routine set of blood tests is carried out: haemoglobin (Hb), kidney function tests (sodium, potassium, creatinine), fasting blood glucose, liver function tests (LFTs), cholesterol profile (total cholesterol and triglycerides), glycosylated haemoglobin (HbA1c) and microalbuminuria for known diabetics, and thyroid function tests (free thyroxine and thyroid stimulating hormone) for patients with known thyroid disease. Fasting plasma glucose and HbA1c are repeated at 3-monthly intervals for diabetic patients; urine dipstick is repeated biannually; and cholesterol profile, kidney function tests and microalbuminuria are repeated annually. The other named tests are repeated as required according to clinical protocols.

Medications are those that are considered standard of care in Jordan; most are on the MSF Green List, the list of medications approved for use in MSF projects, with some additions relevant to the local context. Medications are dispensed from the MSF pharmacy, located onsite at each clinic immediately following a medical consultation. Prescriptions are renewed at maximum one-monthly intervals. Patient data are maintained in paper-based purpose-designed chronic care files, which are stored securely at each clinic.

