### 3.4.2 Cohort study main outcome measures

The principal **clinical outcome measures** for patients in the cohort are:

DM: HbA1c < 7 or 8%; proportion of patients meeting individualised target at last visit within the reporting period and trend from baseline

Hypertension: BP < 140/90 mmHg: proportion of patients at target at last visit within the reporting period and trend from baseline

Cardiovascular disease: change in total cholesterol level from baseline

Asthma / COPD: Free from exacerbations / admissions in last six months

The principal **quality of care outcome measures** are the following:

Number/ % of active patients with CVD prescribed a statin during reporting period

Number/ % of patients with CVD prescribed aspirin during reporting period

Number/ % of patients with CVD prescribed at least one anti-hypertensive during reporting period

Number/% of patients with COPD/asthma with inhaler technique check documented

Number/ % of times when appropriate clinical action taken based on clinical or laboratory findings according to guideline (see Annexe 2e for detail)

Description of trends and patient characteristics in programme defaulters and deaths

Proportion of recommended referrals to other services that are appropriate as per guideline

Death is defined as confirmed death reported by family or community member. A defaulter is defined as a patient who has not attended any NCD clinic appointments within the last 90 days, is not known to have died or moved out of the area, and has not been successfully contacted by phone on two occasions by the clinic registrar. The definition was changed in October 2016 to reflect the newly extended appointment interval for stable patients to: two consecutive missed appointments; not known to have died, moved out of the area, or become immobile and ineligible for home care; and has not been successfully contacted by phone on two occasions by the clinic registrar.

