### 3.4.3 Cohort data sources

The cohort will use retrospective routine facility data collected from files of patients admitted from the start of January 2015 to the end of December 2016. Data on costs for the economic analysis will be obtained from logistics supply, accounting and pharmacy records, and from time estimates obtained through observation and discussions with staff (see below for more details).

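### The exercise and smoking indicators in Table 2 count only improvers, at no fixed visit, so ordinary fluctuation in self-report would show as benefit when nothing has changed

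*Protocol*

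**What the plan says.** Table 2 (Section 3.1), in the Clinical Outcomes row for Effectiveness/Quality of Care, lists two behavioural indicators:

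- Exercise: "Number / % of patients who report increased levels of exercise from baseline during reporting period".
- Smoking: "Number / % of patients who report decreased/quitting smoking within reporting period".

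The blood pressure items in the same cell are worded differently: "most recent BP <= 140/90 6 and 12 months post enrolment and trend from baseline". The HbA1c item follows the same pattern. Among the principal outcomes, Section 3.4.2 defines the hypertension measure as the "proportion of patients at target at last visit within the reporting period and trend from baseline".

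On data collection, Section 1.1.6 says that at review visits "health educators record current exercise levels, smoking status and current stage of change". Section 1.1.2 says that health education is given at each clinical contact and that "Prescriptions are renewed at maximum one-monthly intervals". The cohort uses "files of patients admitted from the start of January 2015 to the end of December 2016" (Section 3.4.3). Sections 2, 3.4 and 6 state that there is no comparator group.

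**The concern.** Both indicators run one way. A patient who moves up a level of exercise is counted; one who moves down is not. A smoker who cuts down is counted; one who smokes more, relapses or starts is not. A proportion at target, as used for blood pressure and HbA1c, falls when patients worsen. A count of improvers cannot register worsening at all.

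The indicators also name no visit, so it is unclear which of several records is compared with baseline. The smoking line does not mention a baseline and is not restricted to people who smoked at baseline.

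These are the only quantitative behavioural indicators under Effectiveness. With no comparator, nothing in the design shows what share of improvers to expect from fluctuation in self-report alone. Section 2 commits the study to examining behavioural outcomes and unintended consequences, yet behavioural worsening has no quantitative indicator. Section 6 accepts that quantitative data carry measurement error. Under a one-way count, that error appears as benefit.

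**Working it through.** The protocol gives no expected value, target or sample size for these indicators, so there is no figure to reproduce. The check asks what the exercise indicator would show if no patient's true behaviour changed.

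**From the protocol:** the definitions above, repeated recording at review visits, and no comparator.

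**Assumed, because the protocol does not give them:** the exercise scale, the reliability of the reports, the number of reports per patient (*k*) and the prevalence of smoking. Reporting error is taken as symmetric and redrawn independently at each visit.

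**Two-level item.** Let *a* = 0.4 be the share truly active and *e* the chance of misreport at a visit. Then

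P(at least one improved report in *k*) = (1 − *a*)(1 − *e*)[1 − (1 − *e*)^*k*] + *a* *e* (1 − *e*^*k*).

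With one follow-up this reduces to *e*(1 − *e*), and the chance of a worsened report is the same. For *e* = 0.02: 0.02 × 0.98 = 0.0196. For *e* = 0.20: 0.20 × 0.80 = 0.16.

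With *k* = 12 and *e* = 0.02: 0.6 × 0.98 × (1 − 0.98^12) + 0.4 × 0.02 = 0.588 × 0.2153 + 0.008 = 0.135.

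**Four-level item.** Simulation of 200,000 patients, with a stable underlying value, levels cut at the quartiles, and reliability (ICC) from 0.7 to 0.95.

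| No true change | Up, one follow-up | Down, one follow-up | Up at any of 12 | Down at any of 12 |
|---|---|---|---|---|
| Two-level, 2% misreport | 2.0% | 2.0% | 13.5% | 9.6% |
| Two-level, 5% | 4.8% | 4.8% | 28.2% | 20.5% |
| Two-level, 10% | 9.0% | 9.0% | 42.7% | 31.8% |
| Two-level, 20% | 16.0% | 16.0% | 52.7% | 41.8% |
| Four-level, ICC 0.95 | 13.1% | 12.8% | 37.5% | 37.1% |
| Four-level, ICC 0.9 | 17.6% | 17.5% | 48.1% | 48.0% |
| Four-level, ICC 0.8 | 22.8% | 22.7% | 57.8% | 57.7% |
| Four-level, ICC 0.7 | 26.1% | 26.1% | 62.9% | 62.8% |

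At a reliability of 0.5, below the range used here, the one-follow-up figure would be 30.6%.

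Three results follow.

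1. At a single follow-up the improver share is 2% to 26% with no true change, and an equal share worsens uncounted. Improved minus worsened is zero apart from simulation error.
2. If any favourable report counted, the share would be larger and would grow with the number of visits.
3. Counting both directions is not enough without a fixed visit. On the two-level item with 10% misreport, the any-of-12 net is 42.7% − 31.8% = 10.9 percentage points although nothing has changed.

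**Smoking.** Let *q* be the chance that an unchanged smoker reports cutting down or quitting at a visit. At one follow-up the share of smokers counted is *q*; at any of *k* it is 1 − (1 − *q*)^*k*. For *q* from 2% to 10%, that is 2% to 10% of smokers at one visit, and 21.5% to 71.8% at any of 12. If 30% of patients smoke and all patients form the denominator, multiply by 0.3: 0.6% to 3% at one visit, and 6.5% to 21.5% at any of 12.

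**The case against.** **The counting rule.** A reader might infer that one favourable report at any time in the period is enough. The text does not say so. Section 3.4.2 and the Maintenance row of Table 2 attach the reporting period to the last visit or consultation, so a last-visit reading is at least as available. The choice of visit could also properly be left to an analysis plan that is not shown. This stands, and the any-of-12 columns are therefore not the measure of the problem. They also rest on errors that are independent between visits; a patient who consistently over- or under-reports gains little from extra visits. Section 3.4.1 requires only two recorded visits, so some patients will have a single follow-up.

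**Size.** The protocol does not support a claim that the spurious benefit is large. With a reliable item and one follow-up it is about 2%.

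**Smoking denominator.** It is tempting to say that counting per patient inflates the result. It does the opposite: an all-patient denominator shrinks the apparent benefit. Its fault is that it is hard to interpret.

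**Cholesterol.** The item "Number/% with a reduction of >= 0.5 mmol/L in cholesterol level from baseline 6 and 12 months from enrolment" is also a one-way count, and a reader might extend the point to it. The documents do not support that: its times are fixed, and Section 3.4.2 makes change in total cholesterol from baseline a principal measure, which moves both ways.

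**Other cover.** Section 3.4.5 promises trends in outcome measures from baseline, and the qualitative work explores difficulty with lifestyle change. The promise of trends names neither item, and a trend in a count of improvers is still one-way. Interviews do not supply the missing count.

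**Importance.** Exercise and smoking are not among the principal outcomes in Section 3.4.2, and the protocol disclaims any formal evaluation of effectiveness. This stands and lowers the weight of the point.

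An analysis plan could choose the visit, but to count worsening it would have to go beyond the indicators as the protocol defines them.

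**Conclusion.** The point holds in a limited form. As worded, both lifestyle indicators count improvers only, fix no assessment visit and have no counterpart for worsening. Under either reading of the reporting period, equal movement in both directions would be reported as improvement.

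For exercise, the last-visit reading gives roughly 2% to 26% of patients counted as improved with no true change. That range assumes symmetric error, and either a two-level item with 2% to 20% misreport or a four-level item with reliability 0.7 to 0.95. The any-report reading could give much more, but the protocol does not establish it. The smoking figures are smaller if all patients form the denominator.

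The severity is minor: these are two secondary descriptive indicators, and the remedy is a change of wording.

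**What to change.** Reword the two indicators in Table 2 as follows.

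- Compare baseline with a fixed follow-up, either 6 and 12 months after enrolment or the last visit in the reporting period, as for blood pressure and HbA1c. Restrict the comparison to patients with both records and report how many those are.
- For exercise, report the percentages improved, unchanged and worsened, and the net paired difference with a 95% CI. With *b* improved, *c* worsened and *n* pairs, the difference is (*b* − *c*)/*n*, with standard error √[*b* + *c* − (*b* − *c*)²/*n*]/*n*.
- For smoking, report reduction or quitting among baseline smokers, with increased smoking in the same group and relapse or uptake among those not smoking at baseline alongside.

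No new data are needed, because Section 1.1.6 already has both items recorded at review visits. The headline percentages will become smaller. The net difference removes symmetric reporting noise only. It does not remove social desirability bias or change over time from other causes, and the report should say so.
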